### Quality Control Measures

Research assistants at all sites will be responsible for the following QC measures:

- Contacting all participants who have missed their study appointment.
- Reminding participants of their study appointments, regardless of mode of interview (remote or in-person).
- Ensuring that each data field is filled out appropriately. If a participant does not wish to disclose something, then the research assistant should document this.

;

This study will be conducted in accordance with the following publication and data sharing policies and regulations:

National Institutes of Health (NIH) Public Access Policy, which ensures that the public has access to the published results of NIH funded research. It requires scientists to submit final peer-reviewed journal manuscripts that arise from NIH funds to the digital archive PubMed Central upon acceptance for publication.

This study will comply with the NIH Data Sharing Policy and Policy on the Dissemination of NIH-Funded Clinical Trial Information and the Clinical Trials Registration and Results Information Submission rule. As such, this trial will be registered at ClinicalTrials.gov, and results information from this trial will be submitted to ClinicalTrials.gov. In addition, every attempt will be made to publish results in peer-reviewed journals. Data from this study may be requested from other researchers after the completion of the primary endpoint by emailing [[contact]](mailto:[contact]).

### Timeline of Study Activities

Aim 3: RCT to Test Decision Aid Efficacy

|                                                          | Year 1:
5/1/19-
4/30/20 |  |  |  | Year 2:
5/1/20-
4/30/21 |  |  |  | Year 3:
5/1/21-
4/30/22 |  |  |  | Year 4:
5/1/22-
4/30/23 |  |  |  | Year 5:
5/1/23-
4/30/24 |  |  |  |
|----------------------------------------------------------|-------------------------------|--|--|--|-------------------------------|--|--|--|-------------------------------|--|--|--|-------------------------------|--|--|--|-------------------------------|--|--|--|
| Start-up (finalize materials, IRB approval at all sites) |                               |  |  |  |                               |  |  |  |                               |  |  |  |                               |  |  |  |                               |  |  |  |
| Participant recruitment                                  |                               |  |  |  | COVID DELAYS                  |  |  |  |                               |  |  |  |                               |  |  |  |                               |  |  |  |
| 3-month post-partum follow-up                            |                               |  |  |  |                               |  |  |  |                               |  |  |  |                               |  |  |  |                               |  |  |  |
| Data analysis and Dissemination                          |                               |  |  |  |                               |  |  |  |                               |  |  |  |                               |  |  |  |                               |  |  |  |

406

407  
408

## Variables

| Variable                                                                                                                                                                                                                                          | BL | T1 | T2 | T3 |
|---------------------------------------------------------------------------------------------------------------------------------------------------------------------------------------------------------------------------------------------------|----|----|----|----|
| Primary Outcomes                                                                                                                                                                                                                           |    |    |    |    |
| Participant knowledge about tubal sterilization                                                                                                                                                                                                   |    | X  | X  |    |
| Participant decisional conflict in postpartum contraceptive choice                                                                                                                                                                                |    | X  | X  |    |
| Secondary Outcomes                                                                                                                                                                                                                         |    |    |    |    |
| Contraceptive method selected                                                                                                                                                                                                                     |    | X  | X  |    |
| Participant satisfaction with contraceptive decision making                                                                                                                                                                                       |    |    |    | X  |
| Exploratory Outcomes                                                                                                                                                                                                                       |    |    |    |    |
| Desire for sterilization*                                                                                                                                                                                                                         |    | X  |    |    |
| Contraceptive method used                                                                                                                                                                                                                         |    |    |    | X  |
| Ease in contraceptive decision-making                                                                                                                                                                                                             |    | X  | X  |    |
| Certainty about sterilization decision                                                                                                                                                                                                            |    | X  | X  |    |
| Participant satisfaction with current contraceptive method                                                                                                                                                                                        |    |    |    | X  |
| Participant confidence with contraceptive method(s)                                                                                                                                                                                               |    |    |    | X  |
| Subsequent pregnancy                                                                                                                                                                                                                              |    |    |    | X  |
| Participant satisfaction with sterilization counseling                                                                                                                                                                                            |    |    |    | X  |
| Satisfaction with, Recommendations for, and Learning from the Decision Aid**                                                                                                                                                                      |    | X  |    |    |
| Proportion of intervention group participants who shared the summary sheet with their provider                                                                                                                                                    |    |    | X  |    |
| Proportion of those who signed Medicaid waiver but did not receive sterilization (calculated)                                                                                                                                                     |    |    |    | X  |
| Reason for signing consent form but not having sterilization                                                                                                                                                                                      |    |    |    | X  |
| Reason for not having sterilization (mismatch T2-T3)                                                                                                                                                                                              |    |    |    | X  |
| Reason for not having other contraceptive method (mismatch T2-T3)                                                                                                                                                                                 |    |    |    | X  |
| Shared summary sheet with provider**                                                                                                                                                                                                              |    |    | X  | X  |
| Covariates and Baseline Characteristics                                                                                                                                                                                                    |    |    |    |    |
| Future Pregnancy Desires: Do you want to get pregnant in the future?*                                                                                                                                                                             |    | X  |    |    |
| Intendedness of Current Pregnancy                                                                                                                                                                                                                 |    |    |    |    |
| Right before you got pregnant with this pregnancy, did you want to have a baby at any time in the future?                                                                                                                                         | X  |    |    |    |
| Would you say you got pregnant sooner, about the right time, or later than you wanted?                                                                                                                                                            | X  |    |    |    |
| On a scale of 0-10, where 0 means you were very unhappy to be pregnant and 10 means that you were very happy to be pregnant, tell me which number best describes how you felt when you found out you were pregnant?                               | X  |    |    |    |
| On a scale of 0-10, where 0 means trying hard not to get pregnant, and 10 means trying hard to get pregnant, if you had to rate how much you were trying to get pregnant or avoid pregnancy before you got pregnant, how would you rate yourself? | X  |    |    |    |
| Signed Medicaid consent                                                                                                                                                                                                                           | X  |    | X  | X  |
| Desire for sterilization*                                                                                                                                                                                                                         |    | X  |    |    |
| Thoughts of sterilization before (and reasons for not)                                                                                                                                                                                            | X  |    |    |    |
| Received any provider contraceptive counseling                                                                                                                                                                                                    | X  |    | X  |    |
| Received any provider sterilization counseling during current pregnancy                                                                                                                                                                           | X  |    | X  | X  |
| Received any provider sterilization counseling during a prior pregnancy                                                                                                                                                                           | X  |    |    |    |
| Age                                                                                                                                                                                                                                               | X  |    |    |    |
| Race/ethnicity                                                                                                                                                                                                                                    | X  |    |    |    |
| Relationship status                                                                                                                                                                                                                               | X  |    |    |    |
| Gravida                                                                                                                                                                                                                                           | X  |    |    |    |
| Parity                                                                                                                                                                                                                                            | X  |    |    |    |
| History of abortion                                                                                                                                                                                                                               | X  |    |    |    |
| Medical and mental health history                                                                                                                                                                                                                 | X  |    |    |    |
| BMI                                                                                                                                                                                                                                               | X  |    |    |    |
| Gestational age (less than 24 weeks or not)                                                                                                                                                                                                       | X  |    |    |    |
| Medicaid coverage of the pregnancy                                                                                                                                                                                                                | X  |    |    |    |
| Religion                                                                                                                                                                                                                                          | X  |    |    |    |
| Highest education                                                                                                                                                                                                                                 | X  |    |    |    |
| Health literacy                                                                                                                                                                                                                                   | X  |    |    |    |
| Income/# people in household/federal poverty level                                                                                                                                                                                                | X  |    |    |    |
| Medicaid status                                                                                                                                                                                                                                   | X  |    | X  | X  |
| Contraceptive method history                                                                                                                                                                                                                      | X  |    |    |    |
| In-person or virtual delivery of the Decision Aid                                                                                                                                                                                                 |    |    |    |    |
| Language of the decision aid                                                                                                                                                                                                                      | X  |    |    |    |

Notes: \*this was measured before and after the decision aid for intervention group at at the very beginning of T1 assessment for control group; \*\*this was only measured for the intervention group

409

## Primary Outcome Variables

| Outcome                                                            | Description of Data Collected                                                                                                                                                                                                                                                                                                                                                                                                                                                                                                               | Time Point                   | Variable Structure  | Format for Data Analysis/ Transformations |
|--------------------------------------------------------------------|---------------------------------------------------------------------------------------------------------------------------------------------------------------------------------------------------------------------------------------------------------------------------------------------------------------------------------------------------------------------------------------------------------------------------------------------------------------------------------------------------------------------------------------------|------------------------------|---------------------|-------------------------------------------|
| Participant Knowledge about Tubal Sterilization                    | Participant responses to 10 True/False items adapted from previously published studies of tubal sterilization knowledge and informed by in-depth interviews with women about sterilization decision making. * Items assess knowledge about tubal sterilization and alternative contraception options and will be coded as correct vs. incorrect, with "Don't Know" being coded as an incorrect response. The percentage of correct responses across the 10 questions will be calculated for each participant. The score range is 0 to 100%. | T1: less than 24 weeks gest. | Continuous (0-100%) | Continuous (0-100%)                       |
| Participant Decisional Conflict in Postpartum Contraceptive Choice | Assessed by participant responses to the low literacy version of the Decisional Conflict Scale (DCS). The DCS is a validated measure to assess participants' decisional conflict in medical decision-making. The DCS low literacy version includes 10 items about experience of conflict, with "Yes" = 0, "unsure" = 2 and "No" = 4. All 10 items are a) summed; b) divided by 10; and c) multiplied by 25. Scores range from 0 (no decisional conflict) to 100 (extremely high decisional conflict). †                                     | T1: less than 24 weeks gest. | Continuous (0-100)  | Continuous (0-100)                        |

†User manual - decisional conflict scale. [https://decisionaid.ohri.ca/docs/develop/User\\_Manuals/UM\\_Decisional\\_Conflict.pdf](https://decisionaid.ohri.ca/docs/develop/User_Manuals/UM_Decisional_Conflict.pdf). Published 1993. Accessed August 8, 2022.

## Secondary Outcome Variables

| Outcome                                       | Description                                                                                                                                                                                                                                                                                                                                                                                                                                    | Time Point                   | Variable Structure                    | Structure for Analysis                                                                                                                            |
|-----------------------------------------------|------------------------------------------------------------------------------------------------------------------------------------------------------------------------------------------------------------------------------------------------------------------------------------------------------------------------------------------------------------------------------------------------------------------------------------------------|------------------------------|---------------------------------------|---------------------------------------------------------------------------------------------------------------------------------------------------|
| Contraceptive Method Selected                 | Will determine the proportion of women who select sterilization versus another method of contraception at Time 1. Assessed by participant responses to an item asking which contraceptive method they are planning to use after delivery.

Note: for participants who give multiple methods as their response, they are asked: "which method are you most leaning towards using after the birth of your baby?"                           | T1: less than 24 weeks gest. | Categorical (proportions by category) | Dichotomous (proportion sterilization vs. all other categories)

*Use the primary method identified if participant selects multiple methods |
| Participant Satisfaction with Decision Making | Assessed by participant responses to the Satisfaction with Decision Scale (SWD), a validated 6-item scale measuring participants' satisfaction with healthcare decision making. * The SWD uses a 5-point Likert scale where 1 is "Strongly Disagree" and 5 is "Strongly Agree." A summary score is calculated as an average of all items with a range of 1-5, with a higher score reflecting a higher level of satisfaction with the decision. | T3: 3 months postpartum      | Continuous (1-5)                      | Continuous (1-5)                                                                                                                                  |

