### **Inclusion Criteria**

Women are considered eligible if they are pregnant and <24 weeks gestation; planning to continue their pregnancy; 21-45 years of age; enrolled in or eligible for Medicaid; speak English or, for women recruited in San Francisco, Spanish; and are contemplating sterilization after their delivery. By focusing on women <24 weeks gestation, we hope to capture women who are still deliberating about their post-partum contraception. If the woman is eligible, the Research Assistant reviews the informed consent and receives verbal or written consent from the woman to participate in the study.

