|----------------------------------------------------------------|---------------------------------------------------------------------------------------------------------------------------------------------------------------------------------------------------------------------------------------------------------------------------------------------------------------------------------------------------------------------------------------------------------------------------------------------------------------------------------------------|---------------------------------------------------------------|-----------------------|----------------------------------------------------------------------------------------------------------------------------------------------------------------------------------------------------------------------------------------------------------------------------------------------------------------------------------------------------------------------------------------------------------------|
|                                                                | 
 
ı Female condom
 
ı Sponge, diaphragm, or cervical cap
 
ı Emergency contraception
 
ı Spermicides
 
ı Intrauterine device (IUD)
 
ı Contraceptive patch
 
ı Vaginal contraceptive ring (Nuva Ring)
 
ı Other (Specify): _____
 
ı None
 
ı Don't know or unsure
 
                                                                                                    |                                                               |                       |                                                                                                                                                                                                                                                                                                                                                                                                                |

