### Primary and Secondary Hypotheses

For the following primary and secondary hypotheses, we will conduct an intention-to-treat analysis using linear or logistic regression to test intervention effects controlling for study site. The beta coefficient and corresponding 97.5% confidence interval will be used to assess the effect of the intervention.

- **Primary Hypothesis a:** Compared to women who receive usual care alone, women randomized to the decision aid arm will have greater knowledge about sterilization and alternative options at T1
- **Primary Hypothesis b:** Compared to women who receive usual care alone, women randomized to the decision aid arm will have lower decisional conflict in postpartum contraceptive choice at T1
- **Secondary Hypothesis a:** Compared to women who receive usual care alone, women randomized to the decision aid arm will also be less likely to select sterilization and more likely to select an alternative method at T1
- **Secondary Hypothesis b:** Compared to women who receive usual care alone, women randomized to the decision aid arm will also be more satisfied with their decision at 3-month follow-up (T3)

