- We will also use ordinal regression (using the recoded 3, 4, and 5 values where higher score indicates higher strength of desire but not for/against sterilization) to test intervention effects controlling for study site.

- **Participant Knowledge about Tubal Sterilization at Time 2:** Compared to women who receive usual care alone, women randomized to the decision aid arm will have greater knowledge about sterilization and alternative options at T2.

- ***Sensitivity Analyses:*** We will run sensitivity analyses to test robustness of the intervention effects after adjusting for differences in:
  - Provider sterilization counseling between T1 and T2 (“since our last meeting”)
  - Provider contraceptive counseling between T1 and T2 (“since our last meeting”)
  - Medicaid consent signed between T1 and T2 (“since our last meeting”)
  - Provider sterilization and/or Medicaid consent signed between T1 and T2 (“since our last meeting”)
- **Participant Decisional Conflict in Postpartum Contraceptive Choice at Time 2:** Compared to women who receive usual care alone, women randomized to the decision aid arm will have lower decisional conflict in postpartum contraceptive choice at Time 2
- ***Sensitivity Analyses:*** We will run sensitivity analyses to test robustness of the intervention effects after adjusting for differences in:
  - Provider sterilization counseling between T1 and T2 (“since our last meeting”)
  - Provider contraceptive counseling between T1 and T2 (“since our last meeting”)
  - Medicaid consent signed between T1 and T2 (“since our last meeting”)
  - Provider sterilization and/or Medicaid consent signed between T1 and T2 (“since our last meeting”)
- **Contraceptive Method Selected at Time 2:** Compared to women who receive usual care alone, women randomized to the decision aid arm will be less likely to select sterilization at T2 and more likely to select an alternative method
- **Contraceptive Method(s) Used at Time 3:** Compared to women who receive usual care alone, women randomized to the decision aid arm will be less likely to select sterilization at T3 and more likely to select an alternative method
- **Ease in Contraceptive Decision Making at Time 1:** Compared to women who receive usual care alone, women randomized to the decision aid arm will report greater ease in contraceptive decision making at Time 1

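### The sterilization-versus-everything-else coding tests only half of the contraceptive-method hypothesis: no planned analysis tests whether more women choose an alternative method

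*Combined protocol and SAP*

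**What the plan says.** Secondary Hypothesis a (Primary and Secondary Hypotheses) states that women in the decision aid arm will be "less likely to select sterilization and more likely to select an alternative method at T1". The Exploratory Hypotheses section repeats both halves for the method selected at T2 and for the method used at T3, where the wording is "less likely to select sterilization at T3 and more likely to select an alternative method".

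The T1 row of Secondary Outcome Variables gives the aim as "Will determine the proportion of women who select sterilization versus another method of contraception at Time 1" and the item as "Assessed by participant responses to an item asking which contraceptive method they are planning to use after delivery". The analysis variable is "Dichotomous (proportion sterilization vs. all other categories" (the closing bracket follows). The only coding rule is "Use the primary method identified if participant selects multiple methods". No answer list is printed, and nothing is said about a woman who names no method or has not decided. The T2 row in Exploratory Outcome Measures uses the same collapse, also without a list.

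The T3 row, on methods used, uses the same collapse and does print its answers. They include *None* and "Don't know or unsure".

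The test is a logistic regression on the binary variable, controlling for site, with a 97.5% confidence interval. The raw answers are kept as categories with proportions.

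**The concern.** The two halves of the hypothesis are equivalent only if every woman who does not choose sterilization names another method. Once some answers name no method, sterilization can fall without any rise in alternatives, and the binary variable cannot show which has happened.

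At stake is the interpretation of a significant result. The hypothesis pairs the two halves in one sentence, so a significant odds ratio for sterilization invites the full sentence as the conclusion. The Research Background gives unmet demand for sterilization, with the risk of undesired pregnancy, as one of two competing concerns; the other is poorly informed decisions and later regret. A move from sterilization to a reversible method and a move from sterilization to no method bear differently on those concerns, so the report should keep them apart.

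**Working it through.** **1. What each part of the document takes as the comparison**

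| Place | What stands against sterilization |
|---|---|
| Study Objectives | another method, described as reversible |
| Secondary Outcome Variables, description | another contraceptive method |
| Secondary Hypothesis a; T2 and T3 hypotheses | an alternative method |
| Analysis coding at T1, T2 and T3 | every answer other than sterilization |

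The last row is wider than the first three. No planned analysis has choice of an alternative method as its own outcome.

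**2. Where non-method answers are documented**

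- T3 method used: *None* and "Don't know or unsure" are printed, so the literal coding puts both in the comparison cell. The plan expects such answers, since T3 staff may ask women why they are not using birth control.
- T1 and T2 method selected: no list is printed. Undecided answers are plausible, because Inclusion Criteria aims for "women who are still deliberating about their post-partum contraception", but this is an inference.
- Other items do have a rule for don't-know answers. They are scored incorrect for knowledge, excluded for sharing the summary sheet, set to 0 for pregnancy timing, and kept as a separate level for the signed Medicaid consent. Method selected and method used have none.

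**3. The plan's own figure**

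The Sample Size Calculation covers only the co-primary outcomes. For d = 0.36, two-sided alpha 0.025 and 80% power:

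n = 2(z₀.₉₈₇₅ + z₀.₈₀)² / d² = 2(2.2414 + 0.8416)² / 0.36² = 146.7, so 147 per arm.

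With 15% attrition, 147 / 0.85 = 172.9, so 173. This reproduces the stated 175 closely and is unaffected by this point. The plan gives no rates or power for contraceptive method.

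**4. Illustration with assumed rates (not from the documents)**

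Control: 60% sterilization, 30% named alternative, 10% none or undecided. Decision aid: 45% sterilization. There are 175 per arm, and two-sided alpha is 0.025, matching the 97.5% interval. Site is ignored.

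Power = Φ[(|p₁ − p₂| − 2.2414·s₀) / s₁], with s₀ = √(2p̄(1 − p̄)/n) and s₁ = √((p₁(1 − p₁) + p₂(1 − p₂))/n).

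Sterilization, 60% vs 45%: p̄ = 0.525, s₀ = 0.05339, s₁ = 0.05278. Power = Φ[(0.15 − 0.11966)/0.05278] = Φ(0.575) = 0.72. The odds ratio is (0.45/0.55)/(0.60/0.40) = 0.545. Neither figure depends on where the 15 points go. The named-alternative comparison (alternative versus the rest) does:

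| Decision aid arm: sterilization / alternative / none or undecided | Change in alternative | Power, planned binary test | Power, alternative vs rest |
|---|---|---|---|
| 45 / 45 / 10 | +15 points | 0.72 | 0.75 |
| 45 / 37.5 / 17.5 | +7.5 points | 0.72 | 0.22 |
| 45 / 30 / 25 | 0 | 0.72 | 0.025 (no true difference) |

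In the first row the none-or-undecided share is 10% in both arms and the two halves move together. In the last row the planned test behaves identically although alternatives have not changed.

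The documented case is T3, where attrition applies. With 175 × 0.85 ≈ 149 per arm, s₀ = 0.05786 and s₁ = 0.05720, so the binary test has power Φ[(0.15 − 0.12968)/0.05720] = Φ(0.355) = 0.64, again wherever the points go.

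**The case against.** The strongest reply is that this is a wording mismatch in a secondary outcome. The sterilization half is tested directly. The raw categories are kept, and Descriptive and Baseline Statistics promises proportions with confidence intervals for the secondary outcomes, so a shift to no method could be seen. Indecision is also measured elsewhere: decisional conflict at T1 is co-primary, certainty about sterilization has a three-level multinomial model at T1 and T2, and subsequent pregnancy is recorded at T3. The illustration is assumed, and its last row is a worst case.

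Much of this stands. It rules out three stronger readings that a reader might infer:

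- *That the second half cannot be tested.* It can, because the answers are kept by category. What is missing is a coding rule and a specified analysis.
- *That none and don't-know answers are known to count as alternatives at T1.* The T1 list is not printed. The T1 probe for women who name several methods asks which one they lean towards, so the item may draw a leaning from some undecided women. How often no method is named there is unknown.
- *That the report would state the opposite of the truth.* In the worst row alternatives are 30% in both arms. A claim of more alternatives would be unsupported, not reversed.

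The reply does not remove the mismatch. Decisional conflict, certainty and pregnancy do not say whether a woman chose another method, and descriptive proportions are not a test of a stated hypothesis.

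**Conclusion.** The point holds in a limited form. The planned binary analysis addresses fewer women choosing sterilization. No planned analysis addresses more women choosing an alternative, although the plan hypothesizes it at three time points. The gap is documented at T3 and conditional on an unprinted answer list at T1 and T2.

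Its size depends on how many women name no method and whether that share differs by arm, and the documents give neither. If the share is zero or equal across arms, the problem is absent or small. Under the assumed 60% and 45%, a significant binary result is equally likely (power about 0.72 at 175 per arm) whether alternatives rise by 15 points, 7.5 points or not at all. The co-primary analyses and the sample size are unaffected. The change is worth making because it is cheap and prevents an unsupported secondary or exploratory claim.

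**What to change.** 1. Print the T1 and T2 answer options, and state how none, undecided and don't-know answers are coded.
2. Keep the binary logistic model for the sterilization half.
3. Add a three-level outcome (sterilization; a named alternative method; none, undecided or don't know) in a multinomial model with site, as the plan already does for certainty. Report none and undecided separately as well, since no method may be a deliberate choice.
4. Claim more alternative-method selection only from the named-alternative contrast, taken as the site-adjusted difference in the probability of naming an alternative. The coefficient against sterilization would not do: in the worst row above it corresponds to (0.30/0.45)/(0.30/0.60) = 1.33 although alternatives are 30% in both arms.
5. Use the same coding at T1, T2 and T3. At T3 several methods can be reported, so give a rule for multiple answers, and say where partner's vasectomy belongs, since Study Objectives speaks of reversible alternatives.
6. Label the added contrast supportive.

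The alternative is to limit the hypothesis at all three time points to selection or use of sterilization and drop the second half.

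The cost is SAP wording and recoding of collected answers, with no new data where these answers were recorded. The downside is one extra contrast per time point.
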